### Study design

2.1

This study has been designed as a double-blinded, single-center, randomized clinical trial for investigating the efficacy of PL in immune functions. A total of 30 subjects with reduced immunity will be recruited from outpatients at DUCKMH through advertisements posted on bulletin boards at hospitals and apartments. Recruitment commenced in October 2019 and the trial is expected to end in December 2020. All participants will receive a full written explanation of the study's protocol and an informed consent form.

During screening, medical history within the past 6 months and drugs taken within the past 4 weeks will be recorded. Additionally, blood tests for liver function, complete blood count, and immune function will be performed.

A total of 30 adults with reduced immunity who meet the eligibility criteria for this study will be randomly assigned in a 1:1:1 ratio to treatment group 1 (PL 1000 mg), treatment group 2 (PL 2000 mg), or control group (placebo). The intervention will begin within 2 weeks of the screening visit.

Based on their study group, the subjects will be administered PL 1000 mg, PL 2000 mg, or placebo for 8 weeks. The total duration of the clinical trial will be 8 to 10 weeks. Subjects will have follow-up visits every 4 weeks, and the efficacy and the safety will be assessed at the second and third visits. The study flow chart is presented in Fig. 1.

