### Sample size calculation

2.3

We have demonstrated in both in vitro and in vivo experiments that PL has immunological effects. To determine the minimum effective concentration, PL was administered at various concentrations, and 200 and 400 mg/kg of PL was administered to mice for 7 days. Based on the United States Food and Drug Administration (FDA)'s guidelines for calculating the effective dose in humans, we used body surface area to translate the effective dose in animal studies to human studies. Based on these calculations, the effective dose in the human body was set at 960 and 1920 mg. For ease of production and intake, the dose was set at 1000 and 2000 mg. According to Whitehead et al^[13]^ in preliminary parallel-designed studies when effect size is considered medium, the empirically optimal sample size is 10 persons per group, due to considerations of feasibility, estimated average, and dispersion accuracy. Therefore, we designed a pilot study with 10 subjects in each group.

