### Statistical analysis

2.8

Statistical analysis will be performed using the principle of full analysis set. For intention-to-treat (ITT) analysis, missing values will be analyzed by last observation carried forward (LOCF). The baseline values before treatment and the changes in NK cell activity at 4 weeks and after treatment will be measured for the 2 experimental groups and the control group. If the data follow a normal distribution, an independent *t* test will be performed to test the differences between 2 groups of continuous variables. If not, Mann–Whitney *U* test will be performed. Paired *t* tests will be performed to test the differences between groups if the data follow a normal distribution. If not, Wilcoxon signed-rank test will be performed. The test of normality for continuous variables will be analyzed using the Shapiro-Wilk test. The confidence level will be set at 5%. All statistical analyses will be performed using SPSS Statistics for Windows Version 20.0 (IBM Corp., Armonk, NY).

Drinking alcohol, which can affect the weekly evaluation, is considered a management variable, and if there is a difference between groups, an analysis of covariance (ANCOVA) will be performed. Descriptive statistics, such as number of subjects, mean, standard deviation, minimum, median, and maximum will be presented for baseline, at each visit, and at final evaluation. Change from baseline to final evaluation will be reported for continuous data, clinical laboratory tests, and vital signs. For categorical data, a division table will be provided. If necessary, 95% confidence intervals will be calculated. No intermediate analysis will be performed.

Demographic variables measured during the screening period will be summarized for each treatment group. Assays for comparison of drug administration groups will be performed. For this purpose, the continuous data will be tested using the *t* test or Wilcoxon rank-sum test. Categorical data will be analyzed using a chi-square test or Fisher exact test.

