The safety assessment will calculate the rate of adverse events. Continuous data, such as comparisons between groups, individual laboratory test results, and biomarkers will be analyzed using paired *t* tests or *t* tests with 95% confidence intervals within the group to see if there are any changes compared with the baseline. If normality is not met, nonparametric statistics (Wilcoxon signed-rank test or Wilcoxon rank-sum test) will be performed. Categorical data will suggest frequencies and ratios for each category. The difference between groups will be analyzed using chi-square test and Fisher exact test.

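### A normality pre-test in arms of 10 picks the test, so results for the two doses and two visits need not rest on the same test or target

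*Protocol article*

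**What the plan says.** Section 2.3 (Sample size calculation) takes from a cited source that "the empirically optimal sample size is 10 persons per group", giving as reasons "due to considerations of feasibility, estimated average, and dispersion accuracy", and concludes: "Therefore, we designed a pilot study with 10 subjects in each group". Section 2.1 (Study design) has two dose arms and one placebo arm in equal numbers.

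Section 2.8 (Statistical analysis) looks at change in NK cell activity at 4 weeks and after treatment. Groups are compared two at a time, by an independent t test when the data are normal and by Mann–Whitney otherwise. The arbiter is named: "The test of normality for continuous variables will be analyzed using the Shapiro-Wilk test". The part of that section on safety, laboratory results and biomarkers has the same switch: "If normality is not met, nonparametric statistics (Wilcoxon signed-rank test or Wilcoxon rank-sum test) will be performed". There, 95% intervals are named alongside the t tests and none alongside the rank tests. For the rest: "If necessary, 95% confidence intervals will be calculated".

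The section does not say whether normality is judged in each arm, in each pair of arms or in all subjects pooled, on values or on changes, or at what level. The Abstract (Methods) names a repeated measures analysis for primary efficacy, which Section 2.8 does not mention.

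**The concern.** The switch is a stated method, so this is not detail left to a fuller plan. Three consequences follow.

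- With 10 values per arm, a normality test has little power, so its result is partly chance. That chance then selects the efficacy test.
- The two dose comparisons with placebo, at two visits, are four separate occasions on which the answer can differ. The t test addresses a difference in means. Mann–Whitney addresses the probability that a subject in one arm exceeds a subject in the other.
- Because the unit of testing is open, a further choice could be made once the data are seen.

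The Discussion expects the study to settle dose and duration, which means reading results across doses and visits. If those results rest on different tests, that reading is harder. Optional intervals also sit badly with a sample size justified partly by accuracy of the estimated mean and spread.

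**Working it through.** **The plan's own figure.** Three arms of 10 give 3 × 10 = 30, as stated. No SD, difference or power is given, so nothing more can be reproduced.

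**Inputs from the document.** 10 per arm; 3 arms; 2 post-baseline visits; t test or Mann–Whitney chosen by Shapiro-Wilk; 5% level for the trial's tests.

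**Assumptions.** Shapiro-Wilk at 5% in each arm; a comparison goes to Mann–Whitney if either of its arms rejects; between-visit correlation 0.6; NK activity normal, or log-normal with log-SD 0.4, 0.6 or 0.8. The document gives no distribution for NK activity.

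**Formulas.** Let r be the chance that one arm of 10 is declared non-normal, the same in all arms.

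- One comparison uses the rank test: 1 − (1 − r)². For normal data r = 0.05, giving 1 − 0.95² = 9.75%.
- The two doses get different tests at one visit (placebo passes, exactly one dose arm rejects): 2r(1 − r)². For r = 0.05 this is 2 × 0.05 × 0.9025 = 9.0%. The maximum is at r = 1/3 and equals 8/27 = 29.6%.
- The four comparisons do not all use one test, if visits were independent: 1 − (1 − r)⁶ − [r + (1 − r)r²]². For r = 0.05 this is 1 − 0.7351 − 0.0524² = 26.2%.

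**Simulation of change scores, beside the formulas** (3,000 to 4,000 trials per row in the runs whose size is recorded; ranges cover repeat runs):

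| NK activity | r per arm | Doses differ at final visit: formula / simulated | Any mix of four: formula / simulated | Verdict differs from a fixed t test, 0.9 SD shift |
|---|---|---|---|---|
| Normal | 5% | 9.0% / 9% | 26.2% / 25–26% | 1% |
| Log-normal 0.4 | 10% | 16.2% / 17–18% | 45.7% / 45–46% | 3% |
| Log-normal 0.6 | 19% | 24.9% / 24–25% | 67.0% / 61–63% | 6–7% |
| Log-normal 0.8 | 29% | 29.2% / 29–30% | 75.0% / 68–71% | 11–12% |

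The simulated mix falls below the formula at larger r because the two visits are correlated and share a baseline.

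**Sensitivity to the reading of the rule.** Here the analysed variable was drawn directly from a named distribution. Any mix of the four comparisons:

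| Distribution | Each arm tested | Each pair of 20 tested |
|---|---|---|
| Normal | 26% | 17% |
| Log-normal 0.5 | 70% | 75% |
| Chi-square, 4 df | 69% | 76% |
| t, 3 df | 64% | 68% |
| Log-normal 1 | 42% | 23% |

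**Type I error of the two-stage rule** (20,000 runs each): 4.9% normal, 5.4% log-normal 0.5, 5.1% log-normal 1.

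**Whether the targets can differ.** Take two log-normal arms with log-SD 1.0 and 0.5, scaled to equal means. The mean difference is 0, yet a subject in the less skewed arm exceeds one in the other with probability 0.63. This is an illustration and not a prediction for NK activity.

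**The case against.** Several stronger readings are tempting, and the objection to each is sound.

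- **No effect estimate when the rank test is used.** A reader might infer this from the optional intervals. Section 2.8 reports number, mean, SD, median and range for each visit, and change to final evaluation, whichever test is used. A mean difference and its interval can be built from these. No between-arm estimate is named for the t test either, and an article may leave the estimator to the full plan. What stands is narrower: intervals are optional for efficacy, and the safety and biomarker text attaches them only to t tests.
- **The doses cannot be compared.** Also too strong. Doses can be compared directly, and each arm's mean and SD are given.
- **Clearly skewed arms usually pass as normal.** In the change-score simulation the arms pass about 90%, 81% and 71% of the time, but those changes are symmetric by construction and only heavy-tailed. Raw skewed log-normal arms pass about 82%, 68% and 53%. Under symmetry and a pure shift both tests address the same shift, so that simulation shows how often tests mix and not how far their targets diverge.
- **The per-arm rule is what the protocol prescribes.** It is an assumption. If each variable were tested once for all arms, both doses would share a test.
- **The mixing rate is the size of the harm.** Counting any mix over four comparisons gives the largest figure. The final-visit and changed-verdict figures are much smaller, and type I error stays near 5%.
- **The switch settles the primary result.** This is not established while the Abstract names repeated measures analysis. Section 2.8 is nevertheless the only detailed text on NK activity, and the switch is worded for continuous variables generally.

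**Conclusion.** The point holds as a matter of interpretation and pre-specification, not of error control. A low-power normality test chooses the method, and the doses and visits need not share a test or a target. With each arm tested at an assumed 5%, tests mix over the four NK comparisons in about 25% of trials with exactly normal data and 45 to 70% under the assumed log-normals. At the final visit the doses differ in test in about 9% and 18 to 30%. The conclusion at a 0.9 SD effect changes relative to a fixed t test in about 1% to 12% of datasets. The normal case needs no assumption about skew and still gives 17 to 26% mixing, depending on whether pairs or single arms are tested. The log-normal figures depend on the assumed spread and correlation.

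The documents do not support reading this as inflated false-positive risk, as absence of any effect estimate, or as making the doses incomparable. For a 30-subject pilot it is a cheap improvement.

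**What to change.** In Section 2.8, including its safety and biomarker text:

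1. Remove the normality switch. Pre-specify one method for all doses and both visits, for example a baseline-adjusted model. Decide any transformation on pooled, blinded data.
2. Replace the optional interval by a between-arm estimate with a 95% confidence interval for every comparison.
3. Give the rank test for every comparison as a sensitivity analysis, not only where normality fails.
4. Keep Shapiro-Wilk, if wanted, as description only.
5. Reconcile Section 2.8 with the repeated measures analysis in the Abstract, so that one primary method is named.

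The cost is wording before unblinding, with no change to recruitment or data collection. The downside is one extra sensitivity table and, if a log scale is chosen, effects that are read as ratios.

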**Methods::**

This study will be a single-center, randomized, double-blinded, and placebo-controlled trial. Study participants will be randomly allocated to 3 experimental groups: those taking PL 1000 mg, PL 2000 mg, or placebo. Total duration of the clinical trial will be 8 to 10 weeks. Study participants will have follow-up visits every 4 weeks and the effect and safety will be assessed at the second and third visits. All participants will be asked to maintain a dosage schedule for this protocol. The primary outcome will be natural killer (NK) cell activity and the secondary outcomes will include peripheral white blood cell (WBC) count; levels of tumor necrosis factor (TNF)-α, interferon (IFN)-γ, and interleukin (IL)-1β, IL-2, IL-6, and IL-12 to assess autoimmune reactivity; and levels of immunoglobulin (Ig)G1, IgG2, and Immunoglobulin M (IgM) to assess allergic activity. Repeated measure analysis will be used to measure primary efficacy based on full analysis set.

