### Outcome measures

2.6

The primary outcome is NK cell activity, which will be used to assess immune reactivity. The secondary outcomes are peripheral WBC count; levels of TNF-α, IFN-γ, IL-1β, IL-2, IL-6, and IL-12 to assess autoimmune reactivity; and levels of IgG1, IgG2, and IgM to assess allergic activity. URI symptoms will also be recorded. All outcome measures will be observed at every visit. For the safety of the participants, we will conduct laboratory tests, such as liver function panels, complete blood counts, and electrolyte levels, and we will evaluate vital signs. Safety assessments will be conducted at the second and third visits. Participants’ data will be anonymized and coded by a specific program.

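### Section 2.8 tests NK activity in three arms at two visits against one unallocated 5% level, names no primary visit or contrast, and disagrees with the abstract on the primary method

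*Protocol article*

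**What the plan says.** Outcome measures (2.6) defines the primary outcome by variable only: "The primary outcome is NK cell activity, which will be used to assess immune reactivity". It gives no visit and no contrast, and adds "All outcome measures will be observed at every visit". Study design (2.1) says that "the efficacy and the safety will be assessed at the second and third visits".

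Statistical analysis (2.8) states that "the changes in NK cell activity at 4 weeks and after treatment will be measured for the 2 experimental groups and the control group". Two groups are to be compared by an independent t test or, without normality, a Mann–Whitney U test; which two groups is not stated. Paired tests follow, with a purpose worded as between-group: "tests will be performed to test the differences between groups if the data follow a normal distribution". The error statement is "The confidence level will be set at 5"%. A later sentence reads "Change from baseline to final evaluation will be reported for continuous data, clinical laboratory tests, and vital signs".

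The abstract's Methods paragraph says something else: "Repeated measure analysis will be used to measure primary efficacy based on full analysis set". Section 2.8 mentions no repeated measures analysis.

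**The concern.** The primary outcome has two active arms, two post-baseline visits and a testing plan built on pairs of groups. Nothing says which comparison decides whether PL worked. A 5% level describes the risk of a false claim only if there is one deciding test, or if the 5% is shared among the tests that can decide. Section 2.8 provides neither. The abstract's repeated measures analysis could supply a single deciding test, but the analysis section leaves it out.

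The wording is also wrong. A confidence level of 5% cannot stand beside the 95% confidence intervals planned in the same section, so the 5% must be a significance level.

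What is at stake is how the result may be worded. With 10 subjects per arm, one chance difference among several could be reported as the primary finding, with 5% quoted as its error rate.

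**Working it through.** **Inputs from the protocol.** Three arms allocated 1:1:1 with 10 subjects each (2.1, 2.3); change in NK activity at week 4 and after 8 weeks of treatment (2.8); two-group tests; one 5% level; no interim analysis (2.8).

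**Assumptions.** Two-sided tests; normal data; pooled t tests on 18 df; no effect of either dose; correlation of 0.5 between the week 4 and week 8 changes, varied from 0 to 0.9. The protocol gives no such correlation.

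**Step 1: the plan's own figure.** For one test the error is 1 − (1 − 0.05) = 5%. Simulation of a single t test with 10 per arm gives 4.9 to 5.0%. So 5% is correct for one test.

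**Step 2: independence as a reference.** For k independent tests, the chance of at least one false positive is 1 − 0.95^k:

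- k = 2: 9.75%
- k = 3: 14.3%
- k = 4: 18.5%
- k = 6: 26.5%, with a Bonferroni bound of 6 × 5% = 30%

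The real tests share arms and subjects, so these values are somewhat too high.

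**Step 3: simulation with the shared arms and the visit correlation** (100,000 null trials):

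| Tests that could support a claim | Number | At least one false positive | Correlation 0.9 to 0 |
|---|---|---|---|
| Each dose vs placebo, week 8 only | 2 | 9% | does not apply |
| All three pairs, week 8 only | 3 | 12% | does not apply |
| Each dose vs placebo, both visits | 4 | 16% | 13 to 17% |
| All three pairs, both visits | 6 | 21% | 17 to 23% |
| Previous row plus paired tests within the two PL arms, both visits | 10 | 29% | see below |

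The last row stays at 29% when the correlation between the raw measurements (baseline, week 4 and week 8) is varied from 0 to 0.9. That variation leaves the correlation between the two changes at 0.5.

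**Step 4: after the change.** Two week 8 contrasts at 0.025 each have a family-wise error of at most 2 × 0.025 = 5%; if independent, 1 − 0.975² = 4.9%.

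**Step 5: price of the change.** The two-sided Dunnett critical value for two contrasts on 27 df is 2.33. The unadjusted t value is 2.10 on 18 df (two-group test) or 2.05 on 27 df (common model). The ratios are 2.33/2.10 = 1.11 and 2.33/2.05 = 1.14. Bonferroni on 18 df needs the 98.75th percentile of t, 2.445, against 2.101, a ratio of 1.16.

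**The case against.** **Detail left to the full protocol or SAP.** A condensed article may leave alpha allocation to a document not shown here. That excuses silence, but 2.8 is not silent. It chooses two-group tests for a three-arm trial, takes two visits and sets one level. It also conflicts with the abstract and misnames the level. Those are defects in the text itself.

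**All pairs, each at 5%.** A reader might infer that every pairwise comparison at both visits is planned at 5% apiece. The text leaves the pairs open and does not say whether the 5% is per test or overall. The Discussion's aim of finding the dose and duration makes such comparisons plausible, but they remain a reading. This part of the objection stands, so the size must be given by reading.

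**A headline of 16 to 29%.** This is also tempting, but neither end is fixed. The lower end ignores the reading in which week 8 is the main time point, which gives 9 to 12%. The final-evaluation sentence in 2.8 points that way, although it concerns reporting and does not designate a primary visit. The upper end needs within-arm paired tests, whereas 2.8 words its paired tests as between-group. A within-arm change is also not a comparison with placebo.

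**Secondary outcomes.** One could multiply 11 outcomes by 3 pairs and 2 visits to get 66 tests and 66 × 0.05 = 3.3 expected false positives. The protocol does not say that the secondary outcomes will be tested in all pairs at both visits, so this figure is not relied on.

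**Repeated measures.** A single global test from the abstract's analysis would hold 5%. That is correct, but 2.8 does not contain it.

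**Pilot status.** The trial is called a pilot, and its size rests on feasibility and estimation. This stands and lowers the severity. It does not remove the point, because the Introduction states the aim as verifying safety and efficacy.

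**Conclusion.** The point holds at moderate severity. The 5% level is not tied to a primary visit, a primary contrast or a set of tests, and the two descriptions of the primary analysis do not agree. None of the separate-test readings examined keeps the chance of a false NK claim at 5%: even the narrowest, two dose-placebo tests at week 8, nearly doubles it.

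All of these figures assume that any one significant test may support an efficacy claim. The protocol states no success rule that either confirms or excludes this. They also rest on normal data and t tests, and those spanning both visits rest on the assumed visit correlation. The finding bears on how an efficacy claim may be worded, not on whether the pilot is worth doing.

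**What to change.** 1. In 2.6 and 2.8, name NK activity at week 8 as the primary endpoint and each PL dose versus placebo as the two primary contrasts, at a two-sided family-wise significance level of 5%.
2. State the procedure: Dunnett from the common model, or Holm or Bonferroni. Holm and Bonferroni also cover the Mann–Whitney branch; parametric Dunnett does not.
3. Report week 4, 1000 versus 2000 mg, within-arm changes and all secondary outcomes as supportive, by estimates with 95% confidence intervals and without efficacy claims.
4. Reconcile the abstract with 2.8, for example by putting the repeated measures model into 2.8 and taking the two week 8 contrasts from it.
5. Replace the term confidence level with significance level, and correct the stated purpose of the paired tests.

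The change is to wording only and needs no further subjects or measurements. The two primary intervals become about 11 to 14% wider with Dunnett and about 16% wider with Bonferroni. A positive result at week 4 alone would no longer support a claim.

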### Intervention

2.5

All eligible participants will receive treatment according to their allocated group, either PL 1000 mg, PL 2000 mg, or placebo, during the 8-week treatment period. To maintain the double-blinded nature of the study, PL 1000 mg, PL 2000 mg, and placebo will be manufactured to be similar in appearance by Hankookshinyak Pharmaceutical Co. (Nonsan, Republic of Korea) and 2 tablets will be taken orally twice a day. The subjects will be evaluated twice in 8 weeks (at 4 and 8 weeks).

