### Data collection and monitoring

2.7

During the screening period, the subjects will fill out a questionnaire about their sociodemographic characteristics, provide a medical history from the last 6 months, provide a drug history from the past 4 weeks, and undergo laboratory tests. Personal information and data collected during the screening period will be managed by the hospital. Monitoring of data and research performance will be performed regularly by Jeneolurl Bio Taek Co., Ltd. (Pusan, South Korea). The final exam dataset will be accessible to statisticians and key investigators. The results of this study will be published in a peer-reviewed article.

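### Section 2.8 lets an observed difference in drinking decide whether the NK cell comparison is adjusted; adjust for baseline NK activity in one fixed model instead

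*Protocol article*

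**What the plan says.** Section 2.8 makes a two-group test the default between-arm analysis: an independent t "test will be performed to test the differences between 2 groups of continuous variables", with Mann–Whitney as the alternative if a Shapiro–Wilk test rejects normality. NK cell activity is described through its baseline value and its changes at 4 weeks and after treatment.

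The next paragraph brings in covariate adjustment. Alcohol intake "is considered a management variable, and if there is a difference between groups, an analysis of covariance (ANCOVA) will be performed".

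No other covariate adjustment appears in the article. The abstract names a repeated measures analysis for primary efficacy, without any alcohol condition, and section 2.8 does not take that model up.

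Four things are left open: when drinking is recorded, how a difference is judged, which covariates besides alcohol would enter the ANCOVA, and whether the ANCOVA replaces the t test or accompanies it. Among the screening items in section 2.7, "the subjects will fill out a questionnaire about their sociodemographic characteristics, provide a medical history from the last 6 months"; alcohol is not mentioned there.

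**The concern.** The decision to adjust should rest on whether a covariate predicts the outcome, and it should be taken before the data are seen. Here it rests on whether the arms happen to differ. What this does depends on the timing that the article leaves open.

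- **Drinking recorded before randomisation.** Any difference between arms is chance. Adjusting only when it appears forgoes the precision that a fixed adjustment would give in every trial.
- **Drinking recorded during the study.** The stated reason, "Drinking alcohol, which can affect the weekly evaluation", leans this way. If treatment or its tolerability changes drinking, the unadjusted comparison estimates the total effect of treatment, while the adjusted one estimates the part that does not run through drinking. A rule that picks one or the other from the data estimates neither consistently.

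In both cases the covariate most likely to help, baseline NK activity, is not named as one. With 10 participants per arm, precision is the scarce resource.

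**Working it through.** The plan gives no figure for this rule, so there is none to reproduce. The sample size is consistent: 3 arms × 10 = 30 (sections 2.1 and 2.3).

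**Inputs.** From the documents: 10 per arm and a 5% level. Assumed: two-sided tests, normal data, one pair of arms, effects in SD units of NK activity, a difference in drinking judged by a t test at 5%, and ANCOVA replacing the t test when that test is significant. The correlations r are also assumptions. Simulated results use at least 100,000 trials per setting.

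**Step 1: how sensitive the trigger is.** The noncentrality parameter is d × √(10/2) on 18 degrees of freedom. A true drinking difference of 0.5 SD is declared in about 19% of trials and one of 0.8 SD in about 40%. With no true difference, one pairwise test triggers in 5%.

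**Step 2: drinking unaffected by treatment.** The two-stage rule is compared with an ANCOVA on alcohol that is always fitted. Power is at a 1 SD effect.

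| r (alcohol, NK) | Type I error, two-stage | Power, two-stage | Power, always ANCOVA | Difference (points) |
|---|---|---|---|---|
| 0.2 | 0.050 | 0.557 | 0.553 | −0.4 |
| 0.3 | 0.048 | 0.556 | 0.574 | 1.8 |
| 0.4 | 0.046 | 0.561 | 0.611 | 5.0 |
| 0.5 | 0.043 | 0.561 | 0.657 | 9.6 |
| 0.7 | 0.037 | 0.570 | 0.815 | 24.5 |

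Type I error stays at or below 5%. The cost is power, and it is small unless alcohol predicts NK activity fairly strongly.

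**Step 3: drinking lowered by treatment.** Suppose treatment lowers on-study drinking by 0.8 SD and has a direct effect of 1 SD on NK activity. The unadjusted estimate then averages 1 − 0.8r.

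| r | Unadjusted, 1 − 0.8r | ANCOVA on drinking | Two-stage rule |
|---|---|---|---|
| 0.3 | 0.76 | 1.00 | 0.905 |
| 0.5 | 0.60 | 1.00 | 0.839 |
| 0.7 | 0.44 | 1.00 | 0.776 |

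The two-stage average matches neither column. The ANCOVA column recovers the direct effect only because the simulation contains no other common cause of drinking and NK activity.

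**Step 4: what baseline NK would give.** Take equal SDs at baseline and follow-up and a baseline–follow-up correlation ρ. The SD of change is √(2(1 − ρ)), so a 1 SD effect becomes 1/√(2(1 − ρ)) on the change scale: 0.845, 1.000 and 1.291 for ρ = 0.3, 0.5 and 0.7.

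| ρ | Power, t test on change | Power, ANCOVA on baseline NK | Gain (points) |
|---|---|---|---|
| 0.3 | 0.432 | 0.576 | 14.4 |
| 0.5 | 0.562 | 0.657 | 9.5 |
| 0.7 | 0.779 | 0.815 | 3.6 |

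ANCOVA on baseline NK is ahead at each assumed value.

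**The case against.** The defence has real force on several points.

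- **Timing.** The article never says that alcohol is an on-treatment measure. The screening questionnaire's items are not listed in full, so a baseline measure is possible. Nothing in the article suggests that the product changes drinking. The mixing of two quantities is therefore conditional, not established.
- **Pre-test and replacement.** The text speaks of a difference, not a significant one, and does not say that the ANCOVA displaces the t test. It could be a supporting analysis. The calculations above assume a formal test and replacement.
- **Baseline NK.** It is used, through change scores. Naming it as a covariate is an efficiency gain, not the repair of an omission.
- **The reference to a weekly evaluation.** Visits are at weeks 4 and 8 (section 2.5), so the phrase is loose. It may simply mean those visits, and nothing in the analysis turns on it.

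A reader might also infer three stronger things that the documents do not support.

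- **The rule inflates false positives.** It does not when treatment leaves drinking unchanged (step 2).
- **A chance trigger switches the quantity being estimated.** Three pairwise 5% tests with no true difference would trigger in about 12% of trials. In that situation, however, both analyses target the same effect under a linear model. The switch arises only when treatment alters drinking, and the 12% does not apply there.
- **The shift on adjustment is a bias.** A just-significant gap is 2.101 × √(2/10) = 0.94 SD. With assumed slopes of 0.2 to 0.4, adjusting moves the estimate by 0.19 to 0.38 SD. If the imbalance is chance, that movement is a correction, not a distortion.

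What stands is the rule itself. It is stated in the text, it depends on the data, and defining the word difference more precisely in a fuller document would not remove that dependence.

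**Conclusion.** The point holds in a limited form. Section 2.8 ties its only covariate adjustment to an observed imbalance in a variable whose timing is not given, and this should be changed.

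The harm is modest if drinking is a baseline variable: no type I error inflation, and a loss of 0 to about 5 power points at correlations of 0.2 to 0.4. The loss reaches about 10 points at 0.5 and 25 at 0.7. If drinking is measured on study and treatment affects it, the reported effect has no single meaning; how far it departs from either target depends on assumptions that the documents cannot settle. Separately, adjusting for baseline NK activity instead of testing change scores would gain about 14, 10 and 4 power points at assumed correlations of 0.3, 0.5 and 0.7.

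All of these sizes rest on assumed correlations, normal data, a 1 SD effect and 10 per arm. The pilot purpose lowers the stakes of any single test. It does not justify the conditional rule, because a pilot's estimates should also have a fixed meaning.

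**What to change.** In section 2.8:

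1. Delete the sentence that makes ANCOVA conditional on a difference in drinking.
2. State one pre-specified model for NK cell activity, either ANCOVA or the repeated measures model named in the abstract, with baseline NK activity as a covariate whatever the observed balance.
3. Include alcohol only if it was recorded before randomisation in all participants, and fix that choice in advance.
4. Report drinking during the study by arm, descriptively or in a sensitivity analysis labelled as such.

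The change needs no extra participants or visits, since baseline NK activity is already measured. It costs one residual degree of freedom per covariate: in a three-arm model at one time point, 30 − 3 = 27 becomes 26 with baseline NK and 25 if alcohol is added. Recruitment began in October 2019. If alcohol was not asked at screening, those already enrolled cannot supply a pre-randomisation value, and alcohol should then be left out of the primary model.
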